For the investigation of the scope of WM, the second block of the eye-tracking experiment will follow the standard dual-task design, in which speakers are first asked to memorize a list of words, then describe a picture of simple transitive actions, and finally to recall the memorized list of words [14, 15, 29, 31, 35, 66]. Before seeing a picture, speakers are shown three nouns semantically unrelated to the action in the picture and asked to remember these words (e.g., traditsioon, ‘tradition’, otsing, ‘search’, investor, ‘investor’). The conceptual load is tested by the so-called verb probe task, which means that after describing the picture, the participants are prompted with a verb, for which they are requested to orally recall the three nouns and to indicate whether they all fit with the verb on the screen (see procedures in [29] for the modification of the standard WM task to tap the phonological and semantic retention). For example, the nouns ‘tradition’, ‘search’ and ‘investor’ co-occur and are acceptable with a transitive verb ‘jätkama’ in Estonian (according to the frequency counts in the National Estonian Corpus and the previous norming study). Crucially, the verb probe task is expected to tap the conceptual retention and deteriorate the conceptual planning processes in describing the pictures such that speakers spare time on making the higher-level conceptual decisions and proceed with describing the pictures in a more incremental manner. This means that instead of previewing and conceptualizing all actors in the pictures, speakers will preview and conceptualize only the actors they mention first in their picture descriptions.

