The eye movements in the existing studies are typically investigated as continuously changing functions of time in a fixed time window (from 0 to 400/600/1000 ms of picture presentation) [16–21, 69, 70]. For the purposes of this study, we derive a new relative measure from the eye movements based on what is currently known about eye movement in the linguistic task settings [16–21, 25, 69, 70]. The new metric is based on the notion of gaze that is defined as multiple consecutive fixations directed towards the region of interest [72]. As the clear start of phonological processing is indexed by a long and intense gaze towards the first-mentioned actor/object right before the onset of speech, the new measure takes this long, “naming” gaze as a landmark for the time window between the picture onset and the start of an utterance. In other words, the duration of these naming gazes will be divided by the speech onset latencies based on the following reasoning.

Namely, the time before the naming gaze indexes the time window where the conceptual frame of an incipient sentence is generated. The time after this longest gaze indicates encoding of further aspects of the incipient sentence (possibly the verb or second-mentioned actor). The highly incremental processing entails that after the picture onset, speakers start to encode the first-mentioned actors as soon as possible [18, 36, 69]. Since they might also start their speech early, they may spend most of the time period between the picture onset and the start of an utterance with processing the first-mentioned actors. In other words, the duration of the naming gaze at the first-mentioned actor relative to the speech onset latency is comparably high. Conversely, the weakly incremental planning assumes that speakers also take time for processing second-mentioned actors, such that the naming gaze at the first-mentioned actor starts later [16, 19] and the speech onset may be somewhat delayed. This means that the duration of the longest gaze towards the first-mentioned actor relative to the speech onset latency is rather low. Consequently, the degree of incrementality and the effect of cognitive load on conceptual processing can be inferred from the duration of the naming gaze measured proportionally to the speech onset latency. In particular, the increasing proportional duration of the naming gaze at the first-mentioned actor or object approximates the increase of incrementality in the conceptual planning processes.

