#### Dependent variables

The dependent variables of interest are (i) speech onset latencies, (ii) duration of naming gazes, (iii) duration of naming gazes proportional to their respective speech onset latencies, (iv) the height of sentence-initial pitch peaks as indexed by F0 maxima (v) and the height of sentence-final pitch valleys as indexed by F0 minima.

First, the starts of utterances (in milliseconds) index the speech onset latencies. Second, a gaze is defined as multiple consecutive fixations directed at the AOI [72]. Gaze duration is calculated by subtracting the onset time of the first fixation directed at the AOI from the offset time of the last consecutive fixation directed to the AOI. Typically, before the speech onset, between one and five gazes occur (see Fig 5). The number of gazes usually increases together with the complexity of the visual scene. The data analysis algorithm will compare between the durations of the gazes occurring before the speech onsets and determine the gaze with the maximum duration, i.e., the longest gaze. The naming gaze is reported as missing (NA) when, in the very unlikely case of only one gaze or of two gazes of exactly the same duration, the algorithm cannot detect a gaze with the maximum duration. The longest gaze before the speech onset is called the naming gaze and submitted to further analyses together with its AOI (either agent or patient).

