The first analysis tests the extent to which the proposed verb probe task tapped the conceptual retention. The proportional duration of naming gazes at the first-mentioned actors is assumed to increase under the high cognitive load. Thus, only the main effect of cognitive load is expected in this analysis. The second analysis investigates the absolute duration of naming gazes, as the interference effect may arise at the phonological planning stage (or semantico-syntactic encoding) instead. In particular, if the phonological encoding of the first-mentioned actors is disrupted due to the memorization of three words the duration of naming gazes right before the speech onsets should increase under the high cognitive load.

The third analysis checks the preliminaries of advance planning of sentence intonation. Namely, the aim is to test how constant the sentence-final low F0 is in the elicited sentences. For this, the statistical evaluation should find no effect of Sentence Length. Nevertheless, the sentence-final low F0 may increase under the high cognitive load, as the existing studies have reported generally higher and flatter F0 contours for speech under mentally challenging conditions [58–64].

Finally, the fourth analysis tests the effect of cognitive load on the scaling of sentence-initial pitch peaks. The significant interaction between Cognitive Load and Sentence Length should demonstrate that the degree of length-dependent pitch raise in sentence-initial pitch peaks depends on the cognitive load. If the cognitive load causes sentence planning processes to proceed incrementally and the incrementality of planning processes mainly bears on the scaling of the pitch peaks, then the sentence-initial pitch peaks are lower under the high load than under the low load, and the difference between the high and low load is greater in long sentences than in short sentences. If the incrementality and the high load both play a role in pitch scaling, then the tonal difference between the high and low cognitive load is expected to occur only in long sentences.

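### The second analysis scores the longest pre-speech gaze but interprets it as the gaze just before speech, so its load effect can partly reflect how many gazes there were

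*Protocol article*

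**What the plan says.** **What is scored.** Under Dependent variables, a gaze is a run of consecutive fixations on one area of interest. The algorithm compares all gazes before speech onset to "determine the gaze with the maximum duration, i.e., the longest gaze". That gaze is named the naming gaze and carried forward with its area, which may be the agent or the patient. On the number of gazes the section says: "Typically, before the speech onset, between one and five gazes occur", and "The number of gazes usually increases together with the complexity of the visual scene". Trials with a single gaze, or with two gazes of equal duration, yield no value: "The naming gaze is reported as missing (NA) when, in the very unlikely case of only one gaze".

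**What it is taken to mean.** The section on theoretical assumptions of the new measure introduces the landmark as "a long and intense gaze towards the first-mentioned actor/object right before the onset of speech". Under Statistical analysis, the second analysis looks for interference at phonological (or semantico-syntactic) encoding of the first-mentioned actors. If encoding is disrupted, "the duration of naming gazes right before the speech onsets should increase under the high cognitive load".

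**What load is expected to do.** The section on theoretical assumptions of the speech production task predicts that, under the memory task, "speakers will preview and conceptualize only the actors they mention first in their picture descriptions".

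**What the model adjusts for.** Block and trial number are the only covariates. Where the four outcomes are listed, the first-mentioned actor is attached to the proportional duration but not to the absolute duration used in the second analysis.

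**The concern.** The scored gaze is defined by rank (longest of all), while the interpreted gaze is defined by position and target (first-mentioned actor, just before speech). The two coincide only when the gaze before speech is also the longest.

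The longest of k gazes tends to be longer when k is larger, even if no gaze has changed. The document says k varies and predicts that load changes how much is previewed, so the compared conditions can differ in k. The load coefficient then mixes the length of the naming gaze with the number of gazes available to choose from.

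Of the four main analyses, the second is the one offered to detect interference at the naming stage. If load reduces the number of gazes, as the protocol's reasoning implies, a true lengthening could be missed and the null read as no interference. If load increases the number, a lengthening could appear without any change at the naming stage.

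**Working it through.** The protocol gives no figure for gaze length, spread or count, so there is no stated result to reproduce. The check asks how far a maximum moves with k.

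**Inputs from the document:** k typically 1 to 5; one-gaze trials set to missing, so the usable range is k = 2 to 5; 84 subjects; 64 target trials each, 32 per load level.

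**Assumptions:** independent lognormal gazes; one naming gaze with mean r × 300 ms and k − 1 other gazes with mean 300 ms; CV 0.3, 0.5 or 0.8; r = 1, 2 or 3.

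**Step 1: expected longest gaze (ms), E[max(naming, others)], by simulation.**

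| r | CV | k=2 | k=3 | k=4 | k=5 | rise, k=2 to 5 |
|---|---|---|---|---|---|---|
| 1 | 0.3 | 349 | 378 | 397 | 412 | 18% |
| 1 | 0.5 | 378 | 427 | 462 | 489 | 29% |
| 1 | 0.8 | 415 | 491 | 549 | 596 | 44% |
| 2 | 0.3 | 603 | 606 | 609 | 611 | 1% |
| 2 | 0.5 | 621 | 638 | 652 | 664 | 7% |
| 2 | 0.8 | 656 | 700 | 737 | 768 | 17% |
| 3 | 0.3 | 900 | 900 | 901 | 901 | 0.1% |
| 3 | 0.5 | 907 | 913 | 918 | 923 | 2% |
| 3 | 0.8 | 933 | 960 | 983 | 1004 | 8% |

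**Step 2: a modest difference in count.** With mean gazes of 400–600 ms (assumed), a 200 ms shift in speech onset changes the count by 200/600 to 200/400, or 0.33 to 0.5 gazes. Take 0.4. One gaze more than k = 2 adds 28–76 ms at r = 1, 3–44 ms at r = 2 and 0.3–27 ms at r = 3 (differences taken before rounding). Multiplying by 0.4 gives 11–30, 1–18 and 0–11 ms.

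**Step 3: against the precision of the load contrast.** With two-thirds of trials usable, n = 84 × 64 × 0.67 = 3,602. With trial SD 250–300 ms and subject slope SD 0–100 ms (assumed), SE = √(4·SD²/n + slope²/84):

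- lower end: √(4 × 250²/3,602) = 8.3 ms
- upper end: √(4 × 300²/3,602 + 100²/84) = 14.8 ms

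This omits item slopes. If trial number runs across the whole session, its squared correlation with a first-half/second-half load factor is 0.75. The variance inflation is then 1/(1 − 0.75) = 4, and the SE is up to twice as large.

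**Step 4: effect on the test.** The within-subject load contrast was simulated with a t-test on subject differences standing in for the mixed model. It used CV 0.5, 24 usable trials per load level, a between-subject SD of the load effect of 30 ms, and 400 runs per cell.

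- *Masking (the direction the protocol predicts), 60 subjects.* With the naming gaze truly 30 ms longer and half of high-load trials losing one gaze, detection falls from 34% to 3% at r = 1, from 54% to 29% at r = 1.5, and from 52% to 36% at r = 2.
- *Mimicking, 84 subjects.* With no gaze changed and half of high-load trials gaining one gaze, a false increase is declared in 84% (r = 1), 33% (r = 1.5) and 12% (r = 2) of runs. The nominal rate in that direction is 2.5%.

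**The case against.** The strongest reply is that the protocol expects the naming gaze to be clearly longer than preview gazes. It describes attention as split between actors in the first 400–600 ms, with long viewing times later, and uses the long gaze as a landmark for that reason. This stands as a limit on size: at three times the length the dependence on count is small. But the document calls the metric new and reports no data on that separation. It also encloses two actors in one area of interest, so gazes that are not naming gazes can be long too.

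The rule is also explicit and prespecified. The theory section itself equates the naming gaze with the longest gaze and allows further encoding after it, so the naming gaze need not be the last one. This also stands. It argues against replacing the longest gaze with the last gaze, which brief return glances can contaminate.

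Three stronger readings are tempting but not supported:

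- *The artefact amounts to several standard errors.* That requires naming gazes no longer than other gazes, subject slopes near zero, and no loss of precision from item slopes or the trial covariate. No onset delay is stated anywhere.
- *The plan is set up to produce false interference.* Its own prediction, less previewing under load, points to masking.
- *Scene complexity biases the load contrast.* All target pictures show three actors, and the picture factors are crossed with load. The complexity statement shows only that gaze count varies.

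Finally, the second analysis is a check on where interference arises. The pitch-peak hypothesis is tested in the fourth analysis and does not depend on this measure.

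**Conclusion.** The point holds as a mismatch between the scored and the interpreted gaze, made consequential by an unadjusted gaze count that the protocol expects load to change. Neither a load effect in the second analysis nor its absence can by itself be read as evidence about the naming stage.

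The size is open. It ranges from negligible, if naming gazes are about three times as long as others with a small spread, to large enough to decide the test, if the two overlap in length. All gaze lengths, spreads and count changes used here are assumptions. Whether load does change the count can be seen only in the data. This is a cheap improvement to one of the four main analyses; it does not make the design invalid.

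**What to change.** Under Dependent variables and in the description of the second analysis:

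1. Restrict the second analysis to gazes at the first-mentioned actor's area of interest, as is already stated for the proportional measure. This aligns the target but does not remove the dependence on count, because several gazes can fall on that area.
2. Keep the longest-gaze duration as the measure, and prespecify alongside it (a) the number of pre-speech gazes by load level and (b) the same mixed model fitted to the last gaze at the first-mentioned actor that starts before speech onset.
3. State that a load effect, or its absence, will be read as evidence about phonological (or semantico-syntactic) interference only if the two versions agree. Otherwise it will be reported as not separable from gaze count.

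The cost is scripting on fixation data that are recorded anyway, plus slightly more to report. The last-gaze version can pick up brief return glances, which is why it accompanies the longest-gaze version and does not replace it.

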**Fig 5 pone.0259343.g005:**
[figure not shown]
Hypothetical onset latencies (left edge of bars) and duration (widths of bars) of gazes directed to a particular area of interest (e.g., blue refers to the agent initiating and orange to the patient undergoing the action of pulling) during the description of an item ‘man pulling a donkey’ in Estonian. The numbers on the squares count the gazes. The black vertical line indicates the speech onset latency. The red ellipse highlights the gaze that is called ‘naming gaze’ and defined as a gaze of longest duration prior to the start of an utterance. For assessing the degree of incrementality, the duration of the naming gaze is divided by the speech onset latency (for similar analysis procedures and data see, e.g., [19]).

Finally, F0 maxima and F0 minima are automatically extracted within the boundaries of agent and patient names and the boundaries of sentence-final words in cases where patient names do not occur at the end of a sentence (e.g., some sentence modifier (e.g., varsti, ‘soon’) follows the patient name). F0 maxima and minima measured in hertz (Hz) will be converted into semitones relative to speaker means based on Eq (1)
$$\begin{array}{c} F0_{st}=12*log_{2}\left(\frac{F0_{Hz}}{F0_{mean}}\right), \end{array}$$
(1)
where *F*0_*mean*_ is the subject’s mean F0 aggregated over all F0 contours extracted from all of the subject’s utterances. This method of converting F0 into semitones has the benefit of partly cancelling out the large-scale, gender-based differences in voice pitch (males typically have lower voice pitch than females). The effect of sentence length on sentence-initial pitch peaks is expected to be smaller than the gender effect. When gender variation in voice pitch is included in the data, the critical effects of sentence length and WM may remain unrevealed.

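### Coding the naming gaze as missing when only one gaze occurs contradicts the protocol's own definition and makes missingness depend on the outcome in the two gaze models

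*Protocol article*

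**What the plan says.** Under Dependent variables the protocol article gives the definition: "The longest gaze before the speech onset is called the naming gaze". The same paragraph states the exception: "The naming gaze is reported as missing (NA) when, in the very unlikely case of only one gaze" or an exact tie between two gazes, the algorithm cannot find a maximum. Shortly before, it gives the usual range: "Typically, before the speech onset, between one and five gazes occur".

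The incrementality measure follows in the legend of Fig 5: "the duration of the naming gaze is divided by the speech onset latency". The section on the new measure of cognitive difficulty explains what a high value means. Highly incremental speakers start encoding the first-mentioned actor early, and "they may spend most of the time period between the picture onset and the start of an utterance with processing the first-mentioned actors". The section on the speech production task predicts that under the memory load, "instead of previewing and conceptualizing all actors in the pictures, speakers will preview and conceptualize only the actors they mention first". Under Statistical analysis, the first model tests whether the proportional duration rises under high load, and the second tests the absolute duration.

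On missing data, the section on pre-processing and data harvesting says that no treatment is needed because the mixed-model method is robust to unbalanced data.

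**The concern.** The rule excludes a case that the definition already covers: when there is one gaze, that gaze is the longest. The only reason given is that the algorithm cannot detect a maximum. That is a property of the script and gives no scientific ground for discarding the trial.

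The discarded trials are not a random subset. A speaker who looks only at the first-mentioned actor before speaking shows the behaviour that the protocol calls strongly incremental and expects more often under load. Whether a trial is kept then depends on the value being analysed. Robustness to unbalanced data means tolerance of unequal cell counts and of missingness explained by what is in the model. It does not cover missingness that depends on the outcome itself, given load, length, subject and item.

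At stake is the first analysis, which checks whether the verb probe task reached conceptual planning. A weakened load effect there would weaken the incrementality reading of the pitch results. The absolute-duration model loses the same trials.

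**Working it through.** The document gives no share of single-gaze trials and no mean or SD of the ratio, so there is no stated figure to reproduce. Every input below is an assumption.

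**Where a single-gaze trial sits on the scale.** Trials are excluded if the first fixation on the area of interest comes later than 400 ms. If a sole gaze starts by 400 ms and lasts until speech onset at latency L, the ratio is at least (L − 400)/L. For assumed latencies of 1500, 1800 and 2000 ms this is 1100/1500 = 0.73, 1400/1800 = 0.78 and 1600/2000 = 0.80. Values of 0.8 and 0.9 are used below.

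**Mixture calculation.** Let pL and pH be the single-gaze shares under low and high load, s the mean ratio in single-gaze trials, and mL and mH the mean ratios in the other trials.

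- Load effect with all trials: [pH·s + (1 − pH)·mH] − [pL·s + (1 − pL)·mL]
- Load effect under the NA rule: mH − mL

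With s = 0.9, mL = 0.45, mH = 0.50, the NA rule always gives 0.050. For shares of 5% and 10%, all trials give (0.090 + 0.450) − (0.045 + 0.4275) = 0.0675, and 0.050/0.0675 = 0.74.

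| Share low / high load | All trials | NA rule | Kept |
|---|---|---|---|
| 0.5% / 1% | 0.0518 | 0.0500 | 97% |
| 2% / 4% | 0.0570 | 0.0500 | 88% |
| 5% / 10% | 0.0675 | 0.0500 | 74% |
| 10% / 20% | 0.0850 | 0.0500 | 59% |
| 5% / 5% | 0.0475 | 0.0500 | 105% |
| 10% / 5% | 0.0250 | 0.0500 | 200% |

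With s = 0.8 the first four rows keep 98%, 91%, 80% and 67%. If mL = mH, so that load acts only by producing more single-gaze trials, the effect under the NA rule is 0 in every row.

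**Simulation with a graded effect.** The ratio was logit-normal (mean −0.2 and SD 0.9 on the logit scale), load shifted it by 0.1, 0.2 or 0.4, and the probability of a single gaze rose with the ratio. There were 2,000,000 trials per load level.

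| Single-gaze shares, low to high load | Kept |
|---|---|
| about 2–4% | 95–96% |
| about 6–11% | 89% |
| about 12–20% | 82–84% |
| about 22–33% | 75–76% |

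Both checks concern the proportional measure. The absolute-duration model loses the same trials, but no size was computed for it.

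**The case against.** The strongest reply is that the protocol itself calls the single-gaze case very unlikely. Every target picture shows three actors, all of whom must be mentioned, and the number of gazes is said to rise with scene complexity. One gaze can be the lower end of a general range and still be rare here. If so, the loss is a few percent. This stands as a limit on size. It does not justify the rule, and the document gives no rate to support it.

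A single-gaze trial is also not always a strongly incremental one. A gaze is defined as multiple consecutive fixations, so on that wording a lone fixation on the other actor would not count as a gaze. Actors sharing a role form one area of interest, so one gaze may cover both members of a coordinated phrase. The sole gaze may also fall on the actor mentioned second. These points stand, which is why the claim is limited to a tendency and to sole gazes on the first-mentioned actor.

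The wording could be read as giving NA only when detection fails. However, the sentence names one gaze as such a failure.

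A reader might infer that the rule always pulls the load effect toward zero, or wipes it out. The documents do not support this. The measure is graded, so trials with several gazes carry the predicted effect too, and complete loss requires load to act solely through single-gaze trials. More single-gaze trials under load is the study's hypothesis, and the table shows the direction changing when the shares are equal or reversed.

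**Conclusion.** The rule is wrong as written: it contradicts the definition of the naming gaze and makes missingness depend on the outcome. Attenuation of the load effect follows if single-gaze trials fall mainly on the first-mentioned actor, have high ratios, and become sufficiently more frequent under high load. For the absolute durations the sole gazes must also be long in milliseconds.

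On assumed inputs for the ratio, the loss is about 3 to 12% at shares of roughly 1 to 4% (s = 0.9 and the simulation; 2 to 9% with s = 0.8). It is about 11 to 26% at roughly 5 to 10%. None of these figures can be derived from the document.

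It would also go too far to infer that the pitch findings are biased. The two F0 models, including the key Load by Length test on sentence-initial peaks, do not use the naming gaze and lose no trials to this rule. Only the supporting evidence on incrementality is affected. Severity is moderate.

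**What to change.** Replace the exception with this rule: when exactly one gaze occurs before speech onset, that gaze is the naming gaze and is recorded with its area of interest. It enters the analysis of first-mentioned actors only if it falls on that actor's area. Keep NA for trials with no gaze and for exact ties.

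Report the number of single-gaze trials by Load and Length, so that readers can see how rare they are and whether they shift with load. A sensitivity analysis with these trials set to missing would show how much they matter.

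The cost is one rule in the extraction script and one small table. The change should be made before the gaze data are examined, since a later choice could depend on the results.
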